### Sample size assumption

Under the conditions of the trial, we assumed that the standard 6-month regimen has a 95% or higher sputum culture conversion rate and with estimated 92.5% of that for 4.5-month study regimen based on the published data. The study was designed to determine whether either of the shortened study regimens was not inferior to the control regimen and a margin of noninferiority of 5% was used. With the assumption that as many as 20% of patients will loss to follow-up or not be assessable in the primary analysis, and with the consideration of approximately 5.5% primary drug resistance prevalence, a total target sample size was 3900 patients (1300 subjects per group) would be required to demonstrate noninferiority, with a statistical power of 0.8 and an alpha level of 0.05 (one-sided). Participant recruitment began in August 2016 and is expected to finish in December 2018.

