### Statistical analysis

According to the standard approach of noninferiority trials, the analysis will be conducted with both per-protocol (PP) and modified intention-to-treat (mITT) populations. Noninferiority, defined as a between-group difference of less than 5% in the upper boundary of one-sided 90% Wald confidence interval (which is equivalent to a one-sided significance of 5%) for the proportion of patients with primary unfavorable outcomes, must be shown on both analyses above to declare that either regimen is noninferior. We will use the chi-square test to compare the secondary outcomes of patients’ sputum-culture conversion at the end of 8 weeks (intensive phase) and treatment completion across treatment groups and the log-rank test to compare the time to culture-negative status. Other secondary outcomes will be analyzed with similar methods, including the time to an unfavorable outcome, the outcome at the end of treatment, adverse effect occurring frequency, patients’ adherence and the transition of radiological manifestation. Missing data will be dealt with the last observation carried forward imputation technique. Dropouts and withdrawals from the study will be recorded through the intervention and follow-up periods. When differences in baseline phenotype are present, these differences will be taken into account during analysis of treatment effect between groups, by regarding them as covariates.

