### Outcome measures

The primary efficacy outcome measures include the percentage of participants with treatment failure or relapse by 24 months after the end of treatment, percentage of participants with treatment failure at either 4.5 months or 6 months after randomization. The secondary efficacy and safety outcomes include the time to sputum (both smear and culture) conversion within intensive phase of 2 months and the percentage of participants with sputum conversion (both smear and culture) at the completion of treatment, the number of adverse reactions occurring on treatment and during the follow-up period, adherence to treatment and radiological manifestation transition. Of note, treatment failure was defined as sputum smear positive at the end of treatment and relapse after completion of treatment is defined as at least one positive culture in the scheduled follow-up visits in two years. Participants with negative cultures at the end of follow-up are considered to have had a favorable outcome. For all treatment failures and relapses, one culture of a sputum sample obtained before treatment and one culture of a sputum sample obtained after treatment failure or relapse are planned to store at −80 °C and the samples will be sent to national clinical TB reference lab in Beijing Chest Hospital for further research. The detailed observation schedule is present in Table 3.

**Table 3 Tab3:** Assessment schedule – for all patients recruited

Observation/Investigation		Screening	Treatment Phase (weeks)									Follow-up (Post-treatment phase, months)							
Study visits		0	2	4	6	8	12	16	19	22	26	3	6	9	12	15	18	21	24
Time window (days)			±3	±3	±3	±3	±7	±7	±7	±7	±7	±14	±14	±14	±14	±14	±14	±14	±14
Demographics		X																	
Written or witnessed informed consent		X																	
Patients eligible criteria judgement		X																	
Medical history and clinical assessment		X	X	X	X	X	X	X	X	X	X	X	X	X	X	X	X	X	X
Concomitant diseases and medication taken assessment		X	X	X	X	X	X	X	X	X	X	X	X	X	X	X	X	X	X
Randomized assignment		X																	
Efficacy evaluation																			
Bacteriological test	Sputum smear	X	X	X	X	X	X	X	X	X	X	X	X	X	X	X	X	X	X
	Sputum culture	X	X	X	X	X	X	X	X	X	X	X	X	X	X	X	X	X	X
X-ray		X				X			X		X		X		X		X		X
Safety evaluation																			
Complete blood count		X		X		X	X	X	X	X	X								
Urinalysis		X		X		X	X	X	X	X	X								
Hepatic and renal functions		X		X		X	X	X	X	X	X								

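### Relapse is counted only from cultures at scheduled visits, so a culture-proven relapse found and re-treated between visits can be scored favourable

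*Protocol article*

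**What the plan says.** All the relevant rules stand in the protocol article under Outcome measures.

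- **Primary outcome:** "the percentage of participants with treatment failure or relapse by 24 months after the end of treatment". The Abstract gives the same 24-month window. Neither statement limits relapse to particular visits.
- **Relapse:** "relapse after completion of treatment is defined as at least one positive culture in the scheduled follow-up visits in two years".
- **Failure:** "treatment failure was defined as sputum smear positive at the end of treatment".
- **Favourable outcome:** "Participants with negative cultures at the end of follow-up are considered to have had a favorable outcome".
- **Visits:** Table 3 lists post-treatment visits at months 3, 6, 9, 12, 15, 18, 21 and 24, each ±14 days, with smear and culture at each. Concomitant diseases and medication are also assessed at each.

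Under Sample size assumption, "a margin of noninferiority of 5% was used". Under Statistical analysis, the upper confidence bound for the difference must lie below 5%, and this, "for the proportion of patients with primary unfavorable outcomes, must be shown on both analyses above".

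**The concern.** The operational definition of relapse is narrower than the outcome it is meant to measure. The primary outcome promises every relapse up to 24 months. The definition admits only those that show as a positive culture at one of eight fixed visits. No other component catches the rest: failure is fixed at the end of treatment, and re-treatment for recurrent TB is not part of the unfavourable outcome anywhere in the article.

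Relapse is the component most likely to separate the arms. The Discussion attributes the failure of three earlier trials of shortened fluoroquinolone regimens to more recurrence with the 4-month regimens, despite rapid culture conversion. If that pattern recurs, losing the same share of relapses in each arm removes more events from the shortened arms. The difference then shrinks in the direction that favours a noninferiority claim. Requiring both per-protocol and modified intention-to-treat analyses gives no protection, because both use the same outcome classification.

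**Working it through.** **Step 1: apply the rules to one patient.** Take a patient who is culture negative at month 3, develops symptoms a month later, has a positive culture at the hospital and restarts treatment.

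- Failure: no, because the smear at the end of treatment was negative.
- Relapse: no, because the positive culture did not come from a scheduled visit.
- Month 6 and later: the patient has had about eight weeks of re-treatment by month 6 and may be culture negative then and afterwards. If so, there is no scheduled positive culture.
- Favourable: yes, because cultures are negative at the end of follow-up.

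A bacteriologically proven relapse is scored as a success. Re-treatment would appear in the medication record at the next visit, but no stated rule turns it into an event.

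**Step 2: effect on the difference.** Let a fraction m of relapses be missed equally in both arms, and take all unfavourable outcomes as relapses. With true rates p_T and p_C,

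observed difference = (1 − m)(p_T − p_C).

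**Step 3: effect on the decision.** The article gives no figure for this effect, so there is none to reproduce. Inputs from the document are 1300 per group, 20% lost or not assessable, 5.5% primary resistance, a 5-point margin and one-sided 5% (z = 1.645). The 1300 is taken as given.

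Evaluable per arm: 1300 × 0.80 × 0.945 = 982.8, about 983.

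Assumptions not in the document are m and the true rates of 10% vs 5%, chosen so that the true difference equals the margin and the correct chance of declaring noninferiority is 5%.

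With d the observed difference, t = 0.10(1 − m) and c = 0.05(1 − m):

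SE = √{[c(1 − c) + t(1 − t)] / 982.8}

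P(declare noninferiority) = Φ[(0.05 − d)/SE − 1.645]

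| m | c vs t (%) | d (points) | SE (points) | P(declare noninferiority) |
|---|---|---|---|---|
| 0 | 5.0 vs 10.0 | 5.0 | 1.18 | 5.0% |
| 5% | 4.75 vs 9.5 | 4.75 | 1.16 | 7.7% |
| 10% | 4.5 vs 9.0 | 4.5 | 1.13 | 11.5% |
| 20% | 4.0 vs 8.0 | 4.0 | 1.07 | 23.9% |
| 30% | 3.5 vs 7.0 | 3.5 | 1.00 | 44.1% |

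Example for m = 10%: SE = √[(0.042975 + 0.0819)/982.8] = 0.01127, and (0.05 − 0.045)/0.01127 − 1.645 = −1.20, so P = 11.5%.

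**Step 4: sensitivity to the all-relapse assumption.** If one point in each arm is end-of-treatment failure, which is never missed, P becomes 11.4%, 23.5% and 42.5% for m = 10%, 20% and 30%. The result hardly changes.

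**The case against.** **The phrase may be loose wording.** It can be read as naming the two-year follow-up period, and the Abstract carries no restriction. This is a condensed article, so the full protocol may hold rules for unscheduled visits. That is fair as to forms, schedule columns and procedures, whose absence here is no defect. It does not remove the point, because the article states a definition and that definition excludes off-schedule cultures. If the wording is only loose, the same edit cures it.

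**Few relapses may be lost.** A relapse found soon after a visit might already have been culture positive at that visit. The ±14-day windows let some off-schedule cultures count as the visit. Some re-treated patients will still be positive at the next visit. All of this stands and argues for a small m, which the document does not give.

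**Fixed visits have a merit.** In an open-label trial, symptom-triggered cultures could be ordered more readily in the shortened arms, whereas fixed visits test each arm equally. This stands and shapes the fix.

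**A stronger reading to avoid.** A reader might infer that a regimen truly outside the margin would usually pass once its observed difference falls below 5 points. The decision rule does not support that, because it tests the upper confidence bound. Take true rates of 10% vs 4%. Suppose a share s of relapses is re-treated at a uniformly random time in a 13-week gap and is culture negative after w weeks, so that s(13 − w)/13 is lost. For s = 25%, 50% and 75%, the observed differences are 5.4, 4.85 and 4.3 points with w = 8, and 5.0, 3.9 and 2.9 with w = 4. The expected upper bounds at 983 per arm are 7.2, 6.6 and 5.9, and 6.7, 5.5 and 4.2. Five of the six still fail noninferiority. The exception needs 0.75 × 9/13 = 52% of relapses lost, and neither s nor w is in the document.

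**Conclusion.** The point holds as a defect of definition. As written, a culture-proven relapse found and re-treated between scheduled visits can be classified as favourable, against the stated outcome of relapse by 24 months.

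The direction of the bias is conditional. It runs toward noninferiority if the shortened arms relapse more, which the Discussion supports for earlier 4-month regimens. If the arms relapse equally, the difference is barely affected.

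The size is not known. At a true difference equal to the margin, the one-sided error would rise from 5% to about 11.5%, 24% and 44% if 10%, 20% and 30% of relapses were missed equally in each arm. These figures rest on the assumed m, on 983 evaluable per arm and on all events being relapses. They show that even a 10% loss would roughly double the error. They do not show that the trial will lose that many, or that a clearly inferior regimen would probably pass.

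**What to change.** 1. Remove the limitation to scheduled follow-up visits from the relapse definition. Count as relapse any culture positive for M. tuberculosis from the end of treatment to month 24, at a scheduled or unscheduled visit.
2. Define the favourable outcome as having no such culture, so that the two definitions cannot overlap.
3. State how re-treatment for recurrent TB is classified in the primary analysis. Table 3 already has medication assessed at each follow-up visit, so the information should be at hand. The choice needs thought, because counting every restart of treatment would add clinical diagnoses to a bacteriological endpoint. Accepting other laboratories' records would likewise admit cultures outside the consortium's microbiology quality control.
4. Report a sensitivity analysis that uses scheduled-visit cultures only.

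The cost is a sentence or two in the endpoint definition and one extra analysis. No new sample size formula is needed. Recruitment began in August 2016, so the change falls mid-trial and should be settled before outcomes by arm are examined. The downsides are a few more events in each arm and some risk of unequal symptom-triggered testing in an open-label trial. The sensitivity analysis shows whether the conclusion depends on that.

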**Methods:**

We are conducting a randomized, open-label, controlled, non-inferiority trial involving patients with smear-positive, newly diagnosed DS-PTB cases nationwide to assess the efficacy and safety of two 4.5- month regimens in comparison to the standard 6-month WHO recommended regimen. The regimen used in one experiment group is a 4.5-month fluoroquinolone-containing regimen, which consists of full course of levofloxacin, isoniazid (H), rifampin (R), parazinamid (Z) and ethambutol (E). Regimen used in the second experiment group includes 4.5-month full course of H, R, Z, E with levofloxacin removed. Patients in the control group, receive H, R, Z and E for 2 months, followed by 4 months of H and R. The primary endpoint is treatment failure or relapse within 24 month after treatment completion.

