### Safety Reporting

Adverse events are defined and reported according to the Common Terminology Criteria for Adverse Events 4.03 (CTCAE). An adverse event is categorized as serious if it led to death, permanent or significant disability, a congenital anomaly or birth defect, life threatening, or required hospital admission for management. A data monitoring committee is needed with the consideration of the potential risk of this study at regular intervals during the trial. Interim analysis is planned when one third of enrolled patients have finished treatment. Thus efficacy and safety data of the study will be reviewed. The study can be stopped before reaching sample size if the data monitoring committee recommends termination of the study or termination of one of the treatment regimens due to unacceptable levels of treatment failure, relapse, adverse effect or mortality compared to the control arm. Important protocol modifications during this study will be updated to the trial registry online.

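### A failure or relapse that is culture-negative at month 24 is also classed as favorable, no precedence rule is stated, and death or treatment change is not an event in itself

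*Protocol article*

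**What the plan says.** The abstract of the protocol article gives the endpoint: "The primary endpoint is treatment failure or relapse within 24 month after treatment completion". Outcome measures repeats it as "the percentage of participants with treatment failure or relapse by 24 months after the end of treatment" and then sets three rules:

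- Failure: "treatment failure was defined as sputum smear positive at the end of treatment".
- Relapse: "relapse after completion of treatment is defined as at least one positive culture in the scheduled follow-up visits in two years".
- Favorable: "Participants with negative cultures at the end of follow-up are considered to have had a favorable outcome".

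Statistical analysis states the noninferiority comparison "for the proportion of patients with primary unfavorable outcomes, must be shown on both analyses above", meaning the per-protocol and the modified intention-to-treat (mITT) analyses. It does not say whether an unfavorable outcome means failure or relapse, or means everything that is not favorable. On incomplete data it says: "Missing data will be dealt with the last observation carried forward imputation technique".

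Death is not named as a component of the endpoint in any of these sections. Mortality appears in Safety Reporting, where the data monitoring committee may recommend stopping the study or an arm "due to unacceptable levels of treatment failure, relapse, adverse effect or mortality compared to the control arm".

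**The concern.** The failure and relapse rules look back over the whole course: one qualifying result is enough. The favorable rule looks only at the end. Applied to the same participant they can give opposite answers, and no sentence ranks them. The primary proportion then depends on which sentence the analyst programs.

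The direction of the possible error matters. The article's Discussion attributes the missed noninferiority of three earlier four-month trials to higher recurrence, despite rapid culture conversion on treatment. Relapse is thus the signal that this trial has to detect. A rule that lets a later negative culture cancel a relapse shrinks the difference between arms, which in a noninferiority trial favors the shorter regimens. The trial is open-label, so a choice between the two sentences made after data have accrued would be hard to defend.

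A second gap lies beside the first. Failure needs a smear result at the end of treatment and relapse needs a culture after completion. A participant who dies, or whose regimen is changed, with neither result positive meets neither definition. If the last culture was negative, LOCF as stated could carry it forward to the end of follow-up and produce a favorable outcome.

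**Working it through.** **Step 1. Apply the written rules to participant paths.**

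| Path | Failure | Relapse | Favorable |
|---|---|---|---|
| Culture positive at month 9, negative at month 24 | no | yes | yes |
| Smear positive at end of treatment, culture negative at month 24 | yes | no (if no positive follow-up culture) | yes |
| Death or treatment change, no positive end-of-treatment smear or follow-up culture, last culture negative | no | no | possible through LOCF |
| Death after a positive follow-up culture | no | yes | no, unless a later negative culture is carried forward |
| Treatment change with a positive end-of-treatment smear | yes | depends on cultures | yes, if negative at month 24 |

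The first two paths can occur in practice. Table 3 is headed as applying to all patients recruited and schedules a culture at every follow-up visit to month 24, so someone who relapses early can still supply a month-24 culture.

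**Step 2. Size of the effect if the favorable sentence prevailed.** The plan gives no figure to reproduce here; this is an illustration.

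Inputs from the protocol article:
- 1300 per arm, 20% lost or not assessable, 5.5% primary drug resistance (Sample size assumption). Evaluable per arm: 1300 × 0.80 × 0.945 = 982.8, taken as 983.
- Margin 5 percentage points; Wald upper bound at one-sided 5%, so z = 1.6449 (Statistical analysis).

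Assumed, not in the documents:
- True unfavorable rates of 5% (control) and 10% (4.5-month regimen), a difference exactly at the margin, where the error rate should be 5%.
- A share f of unfavorable cases, equal in both arms, that ends culture-negative and is relabelled favorable.

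Formulas:
- pC = 0.05(1 − f), pT = 0.10(1 − f)
- SE = √{[pC(1 − pC) + pT(1 − pT)]/983}
- P(noninferiority declared) = Φ{[0.05 − (pT − pC)]/SE − 1.6449}

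| f | pC v pT | Difference (points) | SE | P(noninferiority declared) |
|---|---|---|---|---|
| 0 | 5.0% v 10.0% | 5.00 | 0.01183 | 5% |
| 0.10 | 4.5% v 9.0% | 4.50 | 0.01127 | 11% |
| 0.25 | 3.75% v 7.5% | 3.75 | 0.01036 | 33% |
| 0.50 | 2.5% v 5.0% | 2.50 | 0.00855 | 90% |
| 0.60 | 2.0% v 4.0% | 2.00 | 0.00768 | 99% |

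For f = 0.60: SE = √[(0.0196 + 0.0384)/983] = 0.00768, and Φ(0.03/0.00768 − 1.6449) = 0.988.

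In head counts, f = 0.25 means about 12 of 49 control cases and 25 of 98 experimental cases relabelled (983 × 0.05 = 49; 983 × 0.10 = 98).

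**The case against.** The best defense is that the sensible reading is already there. Both statements of the endpoint are cumulative, relapse is an ever-positive rule, and Statistical analysis plans a time-to-unfavorable-outcome analysis, which treats the outcome as a dated event that a later culture does not undo. The favorable sentence can then be taken as describing those who never failed or relapsed. This stands as far as it goes: the harmful reading is the less natural one. It does not remove the conflict, because the favorable sentence as written carries no such condition and the tested quantity is not tied to either reading.

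On deaths and treatment changes, a reader might infer that such participants can never count as unfavorable. The documents do not support that. A death after a positive follow-up culture meets the relapse rule, a treatment change with a positive end-of-treatment smear meets the failure rule, and LOCF could carry a positive result forward as well as a negative one. The sample-size section also foresees participants who are not assessable, so it is not certain that LOCF would be used for all of them. The article is condensed, and the full protocol or analysis plan may classify these cases; the absence of that list is not the point. What stands is that the stated definitions do not make death or treatment change an event, and that LOCF is stated without exception.

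A reader might also object that relapse should not rest on one positive culture. That definition is clear and looks deliberate. Requiring confirmation is a design trade-off, not an error, and is no part of this point.

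Finally, the 99% figure is the top of an assumed range, not an expectation.

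**Conclusion.** The point holds in this form. The outcome rules are not mutually exclusive for a participant who fails or relapses and is later culture-negative, and the primary comparison depends on which rule prevails. This is a conflict between stated rules, not detail left to another document. Death and treatment change are not unfavorable in themselves, and LOCF could render them favorable when the last culture was negative.

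The size is conditional on three things: that the favorable sentence is the one applied, that the true rates are 5% v 10%, and that the relabelled share is the same in both arms. On those terms the nominal 5% error at least doubles even at a 10% share. Neither the share nor the number of deaths and treatment changes can be estimated from the documents, so no single figure should be quoted as the expected effect. Because the conflict sits in the primary endpoint and costs little to remove, it should be settled before any comparative data are seen.

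**What to change.** 1. State that any failure or relapse is final and overrides later negative cultures.
2. Define favorable as no failure or relapse at any time **and** a negative culture at month 24, and tie the unfavorable outcome in the noninferiority test to the same rule.
3. Do not let LOCF classify as favorable a participant who dies or whose regimen is changed for lack of effect. Classify these cases explicitly, for example as unfavorable in the mITT analysis, and state how the per-protocol analysis treats them.
4. Keep the single-positive definition of relapse. If isolated positives are a worry, handle them in a sensitivity analysis at most.

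Cost: the first two items change wording only and use smears and cultures already in Table 3. The third makes event rates slightly higher and requires cause of death and reason for treatment change to be recorded; Table 3 has no dedicated row for either.
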